**IRAS ID: 293809**

Table of Contents

Introduction3

Background/aims3

Methodology6

Data analysis plan24

Process evaluation25

Ethical considerations29

References 30

1. **Introduction**

|  |  |
| --- | --- |

1. **Background and aims**

People with mental health problems find it very hard to find jobs and remain in work [1-3]. Approximately one sixth of workers experience a mental health problem at any one time [4] and anxiety and depression are considered to be responsible for almost half of working days lost in Britain due to health problems [5]. Whilst the total cost to businesses of mental health problems at work is close to £45 billion, the bulk of this is due to presenteeism at approximately £30 billion [5], more than three times the cost of employee absence. Presenteeism is defined as attending work whilst ill and therefore not performing at full ability. It can be both positive and negative and be due to a variety of factors. Compared to people with physical health problems, people with depression who are employed are much more likely to be unemployed at 6 months, or experience high rates of absenteeism, presenteeism or job turnover [6]. This is one reason why the mental health problems are so costly to individuals, employers, the economy and society.

Whilst models such as Individual Placement and Support (IPS) are effective at helping people to obtain work, they tend to be less successful at helping people keep it and are largely focussed on people with severe mental health problems such as Schizophrenia [7, 8]. The largest proportion of employees with mental health problems have mood disorders such as depression, rather than schizophrenia. Their needs and employer views and processes for this group are likely to be different.

The UK Government also has an “Access to Work” programme, which is able to provide grants and also mental health support to people about to start work or in work. Whilst not based in businesses, an Access To Work representative will visit a workplace to assess the person’s need and recommend adaptations and support that can be provided. They do not operate at the interface between businesses and workers, aiming to improve mental health and productivity outcomes [9].

Furthermore, the impact of the COVID-19 pandemic on mental health is a very serious concern. It is predicted that approximately 41.8% of the UK population are at high risk of mental health problems because of the economic vulnerability and negative economic shock as a direct result of the COVID-19 outbreak [10]. Additionally, a recent report by Durcan and colleagues [11], estimated that should the UK experience a recession effect similar to that of the 2008 banking crisis, at least 500,000 more people could experience mental health problems if the economic impact of the pandemic mirrors those of the last recession.

Currently, this is a space where there is an unmet need, and a lack of evidence about what may help. That is, individuals who have been unwell and are receiving some form of treatment already (such as GP contact, Improving Access to Psychological Therapy (IAPT), third sector counselling or input from secondary mental health services) often do not have the support at work to remain engaged and productive in their employed role. This may be particularly the case in Small and Medium sized Enterprises (SMEs) which may not have occupational health departments to rely on to advise and support workers with mental health problems. Furthermore, not all employees would feel comfortable disclosing unmanageable stress or poor mental health to their employers [12].

Businesses and employees may not know how to tackle the presenteeism related to mental health problem, responses need to be framed by the legal framework, there may be conflict between the parties, as well as consequences to work colleagues. One of the largest wellness studies conducted in the UK exploring the link between modifiable health risks and short-term productivity found that the UK economy lost approximately £92 billion as a result of ill-health related absences and presenteeism in 2019 from factors such as depression, poor lifestyle and stress. The study also revealed that British businesses lose on average 37 working days per employee per year due to physical and mental health related absences and presenteeism in 2019. The study revealed a rise in presenteeism with approximately 45% of UK employees admitting suffering from presenteeism in 2019, a two third rise (24%) from 2014. Young workers aged (18 to 25 years) were particularly vulnerable with 55% reporting unable to perform at their peak productivity, compared to 38% of employees aged 45 or over [13]. Traditional healthcare providers alternatively may not have enough knowledge of job roles or business structures to be able to help employers and employees alike adequately and effectively.

In order to address this intervention and evidence ‘gap’ and building on discussions between the partners within the wider research team (including with clinicians and mental health service providers) we propose to innovate and assign a specifically trained Mental Health Employment Liaison Worker to work at the interface between employers, employees and mental health providers. We will test the feasibility and acceptability of this intervention thoroughly as this is a new innovative model meeting a need that is currently poorly served, but potentially critical to improving the wellbeing and mental health of workers. Feasibility and pilot studies are conducted before a main study to address areas of uncertainty that will enable a successful full definitive trial [14] This feasibility pilot study aims to examine the feasibility, acceptability and preliminary estimates of a 3-month Mental Health Employment Liaison Worker (MHELW) intervention in supporting the mental health and productivity of employees with a clinical diagnosis of mental health problems who are working.

**Research Question:**

To test whether the Mental Health Employment Liaison Worker (MHELW) intervention is acceptable and feasible in supporting employees with a clinical diagnosis of mental disorder and currently receiving treatment by an NHS healthcare provider?

1. **Methodology**

Study design: A feasibility randomised controlled trial with a 3-month MHELW intervention supporting workers with a clinical diagnosis of mental disorder to remain engaged and productive compared to control, receiving the intervention after a 3-month delay. The trial will be registered on the ISRCTN registry.

**Population:** Adult workers with a clinical diagnosis of a mental health disorder, who are currently receiving treatment by an NHS healthcare provider.

***Inclusion criteria:***

- Employees with a clinical diagnosis of a mental health disorder
- Employees currently receiving care for mental health problems through NHS services
- Aged ≥18 years
- Able to give written informed consent
- Fluent in English
- Willing to work with the MHELW and their business line manager

***Exclusion criteria:***

- Currently in acute mental health crisis as defined by their clinical team
- Currently on extended sick leave (i.e., >4 weeks)
- Receiving input from an Individual Placement and Support (IPS) Worker
- Planning to retire within the next 10 months and unable to complete intervention and evaluation

**Intervention:** Employment focussed support and input from a Mental Health Employment Liaison Worker (MHELW). The reporting of the intervention will be aligned to the Template for Intervention Description and Replication (TIDier) checklist [15], to ensure that MHELW are consistent and transparent in reporting/documenting each of the 10 intervention sessions across the 3 months study intervention. The MHELW will provide support to employees identified as having clinically significant, mental health problems (i.e., those who are currently receiving statutory NHS treatment), to remain engaged and productive at work. The role of the MHELW will be to liaise between employers, employees and care providers so that businesses and employees can receive dedicated and optimised support and advice on what good workplace wellbeing practices look like for each individual and how stakeholders can help achieve this. This will facilitate the process via which employees can continue to work, and employers can be helped to make this happen, likely reducing the probability that employees then are absent from work.

Depending on the size of the organisation, a MHELW will support several businesses at any one time and be agile on time spent in each business depending on demand. Each trial participant will be supported by an MHELW for a period of three months. A three-month period was selected as it prioritises dynamic facilitation and action in the short term to have an impact and increases the likelihood that the intervention will be cost-effective. Due to the outbreak of COVID-19, MHELWs will provide support both face-to-face and online, due to ongoing home working and social distancing requirements during the pandemic and beyond the operation of the MHELW will need to be implemented across both forms of delivery. The MHELW will not provide formal (e.g., manualised) psychological therapy for employees.

MHELWs will hold 10x1hr sessions across the 3 months, with the option of 3 of these conducted face to face. Then sessions will be made of from: 3 employees only, 3 managers only and 4 joints with both parties. The MHELW is present to identify the accommodations from both employer and employee that could be made for the employee to continue being supported and to continue at work. Employees/line manager will receive a £10 voucher at the end of the study intervention. Further, some participants and line managers who have consented and agreed to take part in the qualitative interview, will also receive an additional £10 voucher. Additionally, the intervention will be free to participant and environmentally friendly, convenient to access, will not require workers to take time off work, and will not require extra travel/costs.

**Pre-screening phase**

After participants register their interest in the study, the research team will contact participants with a link to consent for an online eligibility screener. The online screener contains specific questions to ensure participant fits the study eligibility criteria as described in the inclusion/exclusion. After a short online screener to determine eligibility, employees will be enrolled in the study, however they will have an equal chance of ending up in the waitlist control or the intervention group. Capacity limitations may mean that not all eligible employees will be invited to participate. Employee’s healthcare professionals (HCP) will be notified of their participation in the study. Furthermore, HCP’s will be asked to provide some information about the impact of the intervention on employee’s job and health and wellbeing.

**Role descriptors of the MHELW:**

These are based in part on the Individual Placement Support (IPS) employment specialists and the IPS fidelity scale [16], but with modifications and specifications aimed at supporting people already in employment to maintain this and improve their well-being. These have been developed and refined by Mind (the provider organisation) subsequent to internal Mind stakeholder consultation groups. These descriptors are:

1. An ethos that recovery is likely and therefore work can be maintained

1. Zero exclusion – a person’s desire to continue to be employed is the only criterion for access to the MHELW.
2. The support provided will be based on employee preferences
3. The MHELW will work independent to the business and employee but will focus on both sets of needs-this is based on the idea that it is in the interests of both the business and employee that the individual be supported to continue to work, and their experience of work be improved
4. The support to the business and employee will be individually tailored but will in general terms involve stage 1 (preparatory meetings with both parties where process and desired outcomes are explored), stage 2 (involving tailored support regarding adaptations, education, mental health support), and stage 3 (review of actions and impacts and future planning)
5. Acting as main point of liaison between NHS providers, the business (line manager) and employees subject to consents. In practice this may involve attending joint meetings between the employee and manager or holding individual meetings and advising on what adaptations might be necessary for the worker and supporting these to happen. It may also involve providing feedback to care providers in the form of a report on progress made and topics covered during the intervention, as well as background on the participant’s workplace context (subject to consent).
6. from the business (subject to consent)
7. Monitoring and reviewing adaptations
8. Upskilling the business line manager and employees about the importance of work for mental health by providing relevant mental health education
9. Providing basic mental health support to employees, but not any formal therapy as this might interfere with their current NHS treatment plan
10. High accessibility of help-links with employer platforms, posters, emails sent to staff
11. MHELWs will have initial group training and ongoing group supervision
12. Maximum number of people per MHELW will be 20 (similar to IPS programmes)
13. If one is available, the MHELW will also work with and develop relationships with the occupational department of the business
14. The MHELW will have contact with healthcare providers (subject to consent). Employers will not have access to health records or letters.

During the trial preparation critical components (e.g., training manual) will be manualised to aid implementation and future replication, but also used as a basis to develop the training programme. The intervention will last for a maximum of 3 months-the point at which primary outcome measurements will be taken.

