**Full** **randomised controlled trial sample size**

There have been no previous randomised controlled trial (RCT) studies reporting effect sizes of liaison workers intervention programmes on work productivity. With limited empirical findings to base our sample size calculations on, we estimate a small to medium effect size of (d=0.33). The estimated sample size necessary to detect an effect size (Cohen’s d) of 0.33 at an alpha error rate of 0.05 (two-tailed) and a beta error rate of 0.20 using the G* Power 3 program was 292 participants (146 participants per arm) [17-18]. However, we anticipate we may need to obtain consent from up to 365 participants at randomisation, anticipating a 25% attrition rate. This equates to a N point difference between the arms in our primary outcome measure.

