The process evaluation will use a mixed method approach and use the RE-AIM (reach, effectiveness, adoption, implementation, and maintenance) framework [40]. It will be made up of two parts:

1. **Quantitative data collection:**

During the course of the study and at 3 months after baseline we will measure

- Number of contacts with MHELW
- Length of contacts of MHELW
- Number of contacts between MHELW and NHS providers
- Referrals to non-statutory providers

1. **Qualitative data collection:**

We will conduct a qualitative evaluation aiming to explore engagement, acceptability, barriers, and facilitators, for employees, line managers and MHELWs delivering the intervention. Participants who were selected and agreed to take part in the interview will be sent a consent form and participant information sheet via email. We will explore what have MHELW been asked to do, whether they feel able to complete these actions and what they have felt unskilled for. Qualitative data will be collected from sub- samples of these 3 stakeholder groups using either individual interviews or focus groups depending on acceptability to businesses and workers. These are:

1. Employees (N=16-20) individual interviews,
2. Line Managers (N=16-20) individual interviews
3. MHELWs (N=6-8)-focus group.

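### The full-trial size of 292 assumes independent participants, although intervention participants share liaison workers; the effect on power depends on a caseload and an ICC that the protocol does not give

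*Protocol*

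**What the plan says.** Under the heading on the full randomised controlled trial sample size, the Protocol takes a standardised difference ("we estimate a small to medium effect size of (d=0.33"), an "alpha error rate of 0.05 (two-tailed", and "a beta error rate of 0.20 using the G* Power 3 program". The result "was 292 participants (146 participants per arm". It then allows for "up to 365 participants at randomisation, anticipating a 25% attrition rate". The section mentions no ICC, design effect, caseload or number of workers.

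Other sections describe how the intervention is delivered:

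- Randomisation: individuals are the unit.
- Intervention: one liaison worker (MHELW) supports each participant for three months.
- Role descriptors: support is tailored to the individual, and "Maximum number of people per MHELW will be 20".
- Control group, and Outcomes: Data collection: controls receive the intervention only after a 3-month delay, with no further outcome data collected from them.

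The only indication of worker numbers is in the Process Evaluation, for this pilot's qualitative work: "MHELWs (N=6-8)-focus group".

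**The concern.** Participants who share a liaison worker may have outcomes that are more alike than those of participants with different workers, because skill, style and local contacts differ between workers. Here that can happen only in the intervention arm, since controls have no worker when the outcome is measured. The design is therefore partially nested. The variance of the intervention mean is inflated by a factor that grows with the caseload and the ICC, and a calculation that treats all participants as independent overstates power.

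What is at stake is the planning figure for the later trial. The Protocol publishes 292 and its inflated total of 365, and sets the pilot's recruitment target at 15% of that total. A reader deciding whether a full trial is achievable will take 292 as sufficient for 80% power, and the assumption behind it is not stated.

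**Working it through.** **Inputs from the Protocol.** d = 0.33; two-sided alpha 0.05; power 80%; 146 analysed per arm; at most 20 participants per worker; clustering in the intervention arm only.

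**Assumed, because the Protocol gives no value.** ICC 0.01 to 0.05; mean caseload m of 5, 10 or 20, where 20 is the cap and not an expected value.

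**Step 1: reproduce 292.** The exact two-sample t-test (noncentral t, independent participants) has power 79.97% at 145 per arm and 80.24% at 146. The smallest adequate size is thus 146 per arm, or 292. The Protocol's figure is reproduced exactly. It contains no allowance for clustering, and its margin is only 0.24 percentage points.

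**Step 2: variance under partial nesting.** With total variance 1 in each arm and n per arm,

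- Var(difference) = {[1 + (m − 1)ICC] + 1}/n = [2 + (m − 1)ICC]/n.
- Power ≈ Φ(0.33/SE − 1.96), where SE is the square root of that variance at n = 146.
- Required n per arm = [2 + (m − 1)ICC] × [(1.96 + 0.8416)/0.33]² = [2 + (m − 1)ICC] × 72.07, rounded up.

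Example for m = 20, ICC 0.05: the factor is 2 + 19 × 0.05 = 2.95. SE = √(2.95/146) = 0.142, so 0.33/0.142 = 2.32 and power = Φ(0.36) = 64.1%. Required n = 2.95 × 72.07 = 212.6, so 213 per arm and 426 in total.

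**Step 3: results at 146 per arm.**

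| Participants per worker | ICC | Factor replacing 2 | Power | Total analysed for 80% |
|---|---|---|---|---|
| any | 0 | 2.00 | 80.5% | 290 |
| 5 | 0.01 | 2.04 | 79.7% | 296 |
| 5 | 0.05 | 2.20 | 76.7% | 318 |
| 10 | 0.01 | 2.09 | 78.8% | 302 |
| 10 | 0.05 | 2.45 | 72.2% | 354 |
| 20 | 0.01 | 2.19 | 76.9% | 316 |
| 20 | 0.02 | 2.38 | 73.4% | 344 |
| 20 | 0.05 | 2.95 | 64.1% | 426 |

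Totals are before attrition. The normal approximation starts from 80.5% and 290, so it is slightly more favourable than the exact test in Step 1.

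**Step 4: sensitivity.** With few workers, a t reference with Satterthwaite degrees of freedom gives lower power. At the cap (146/20, about 7 to 8 workers) it is about 73%, 69% and 58% for ICC 0.01, 0.02 and 0.05. At 5 per worker the change is about one percentage point. Applying the design effect to both arms would be wrong here and would exaggerate the loss: 52% instead of 64% at m = 20, ICC 0.05.

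**The case against.** The strongest reply is that 292 is not the size of the trial under review. The Protocol says this study does not test hypotheses, sets its size on pragmatic grounds, and supports it with published recommendations of 24 to 50 per arm. Recruitment, retention, questionnaire completion and session attendance do not depend on full-trial power. This stands. The point concerns only the published planning figure and does not affect the pilot's own size or measures.

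A second reply is that the loss may be small. This also stands in part. The figure of 20 is a ceiling. The 6 to 8 workers in the Process Evaluation are a focus-group size in this pilot; spread over its 28 intervention participants they imply about 3.5 to 4.7 each. If the full trial kept that ratio, power would be about 77% to 80% for ICC 0.01 to 0.05. Manualised components, common training and joint supervision may also keep the ICC low. Baseline adjustment might recover some power, but the sample-size section neither invokes it nor gives a baseline correlation.

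Two stronger readings are tempting, and the Protocol supports neither:

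- **Power near 65% or 60% as the expected result.** This needs about 18 participants per worker, obtained by spreading the full trial's 146 over 8 workers, together with an ICC of 0.05. The Protocol does not state the full trial's number of workers, its expected caseload or an ICC.
- **A type I error of about 10%, or an error in the Data analysis plan because it has no worker term.** The 2 × 2 ANOVA is this pilot's analysis, and the full trial's analysis is not fixed here. At the pilot's likely caseloads the unadjusted error would be about 5.1% to 6.1%, in a study that disclaims hypothesis testing. A worker term may also properly be left to a SAP that is not shown.

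**Conclusion.** The point holds as a limited one about the full-trial figure. The 292 is an independence calculation at its minimum, and it is given for an intervention that the same Protocol delivers through shared workers in one arm. The direction of the effect is clear: apart from a correlation small enough to fit within the 0.24-point margin, any positive within-worker ICC takes power under that calculation below 80%.

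The size of the effect is not known. It runs from negligible (79.7% at 5 per worker, ICC 0.01) to serious (64.1% at the cap, ICC 0.05), and rests wholly on the assumed ICC and caseload. No single value in that range should be quoted as the trial's true power.

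**What to change.** In the full-trial sample-size section:

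- State that 292 assumes no clustering by liaison worker.
- Give power, or required size, over a range of caseload and ICC, using 2 + (m − 1)ICC in place of 2, and label both as assumptions.
- State that the full trial's size and analysis will allow for partial nesting.

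In the pilot, keep the liaison-worker identifier linked to the outcome data through anonymisation, and report the caseload per worker. Any between-worker variation should be descriptive only, because a pilot of this size cannot estimate an ICC with useful precision.

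The cost is a few sentences, a short table and one variable in the dataset. No extra pilot participants are needed, and the feasibility and acceptability measures stay as they are. The downside is that the stated full-trial power falls or its required size rises, which makes the later trial look somewhat harder to deliver.
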